## Abstract

**Background:**

Localised renal cell carcinoma is treated with radical nephrectomy (RN) or partial nephrectomy (PN). Nephron-sparing PN increases preservation of renal function, reducing incidence of end stage renal failure and associated cardiovascular events. In patients with exophytic T1a (≤ 4 cm) tumours and normal contralateral kidney, PN is standard of care. In patients with T1b (> 4–7 cm) or endophytic T1a tumours and normal contralateral kidney, the benefits of PN over RN are less clear as there are increased surgical complications and more tissue may be excised reducing the preservation of renal function. There are no high-quality studies to address if PN is superior to RN in these more complex cases.

**Methods:**

PARTIAL is a pragmatic randomised controlled parallel group unblinded superiority trial with embedded internal pilot and economic and process evaluation. A total of 420 participants will be recruited in UK NHS centres with expertise in minimally invasive nephrectomy techniques. Eligible consenting adults with a single T1 renal cell carcinoma, normal contralateral kidney and equipoise within the multidisciplinary team confirming suitability to receive both interventions by minimally invasive approaches are randomised 1:1 to PN or RN. Patients with metastatic disease, existing chronic kidney disease, solitary functioning kidney, congenital renal abnormality, inherited kidney cancer syndrome, who lack capacity to consent or are pregnant or breast feeding are excluded. Primary outcomes are gains in preservation of renal function at 2 years and surgical complications over the peri-operative period. Secondary outcomes are quality of life and recovery, cost and cost-effectiveness, rates of positive surgical margin, recurrence and cardiovascular events, overall survival, progression to chronic kidney disease and end stage renal failure, operative conversion and patient acceptability. Participants are followed up for 2 years with outcomes collected from medical records and participant questionnaires.

**Discussion:**

PARTIAL will determine if gains from PN are superior to RN and offset the potential harms and costs in complex T1 renal tumours suitable for either approach. If PN is not found to provide clinically significant gains and excess complications are confirmed, then a practice-changing case for RN as standard of care could be made.

**Trial registration:**

ISRCTN 11293415. Registered prospectively on 19 January 2023.

**Supplementary Information:**

The online version contains supplementary material available at 10.1186/s13063-026-09624-4.

## Administrative information

Note: the numbers in curly brackets in this protocol refer to SPIRIT checklist item numbers. The order of the items has been modified to group similar items (see http://www.equator-network.org/reporting-guidelines/spirit-2013-statement-defining-standard-protocol-items-for-clinical-trials/).

## Introduction

### Background and rationale {6a}

Widespread use of imaging investigations has led to a major increase in incidental diagnoses of early small kidney cancers. Incidence has doubled over the last 20 years and is projected to increase further [1]. Kidney cancer is the 7th most common cancer in the UK with over 13,000 new cases per year [2]. Renal cell carcinoma (RCC), the commonest type of kidney cancer, was historically managed by radical nephrectomy (RN) to remove the whole kidney. Most of these patients managed without significant problems with their remaining kidney [3], which partly compensates for the lost function. In those patients with pre-existing chronic kidney disease (CKD) or a solitary kidney, nephron-sparing partial nephrectomy (PN) became the preferred surgical treatment option to remove only the portion of the kidney containing the cancer. PN is technically more challenging and associated with increased surgical complications, positive surgical margins and recurrence rates. However, in situations of renal compromise, these increased risks were offset by maintained renal function that in turn potentially reduced cardiovascular events and helped avoid CKD and end stage kidney disease (ESKD) [4].

Experience of PN has grown and its application has expanded to include small peripheral tumours (≤ 4 cm, T1a) in patients with a normal contralateral kidney. With surgical advances afforded by robotic surgery [5], European Association of Urology and major US guidelines recommend that surgeons tackle intermediate sized tumours (4–7 cm, T1b) and/or higher complexity surgeries involving central (hilar) T1a tumours with PN in those patients with normal contralateral kidney [4, 6, 7]. However, PN to treat larger and/or more complex tumours can be associated with (i) a greater loss of renal mass and renal function and (ii) higher risks of significant perioperative complication and positive surgical margins [8].

Currently, there are no ongoing RCTs of PN vs RN for surgical treatment of smaller renal tumours. Previous evidence syntheses have relied predominantly on retrospective cohort data [9, 10]. A Cochrane review identified the only randomised controlled trial (RCT) comparing PN and RN for small RCCs (< 5 cm) [11]. This RCT did not meet its pre-planned accrual targets and the technical approaches to PN were still being refined. A 21% crossover occurred, mainly PN to RN due to perceived technical challenges, affecting the intention-to-treat analysis [12]. In terms of overall survival, non-inferiority of PN was not demonstrated [13]. Given the absence of high-quality evidence, the authors of the Cochrane review recommended a methodologically rigorous study to assess the potential benefits and harms of PN, whilst accounting for baseline renal function, tumour size and patient age [11]. Technical advances with minimally invasive robotic PN have rapidly progressed and the clinical climate is now receptive to the conduct of an RCT. More recently, < 5% of procedures were reported to convert from PN to RN [14–16].

Following both PN and RN, renal function initially falls but compensations can occur with within the first 9 months after surgery and stabilises beyond the first 12–18 months [3, 17]. In Van Poppel et al., mean estimated glomerular filtration rate (eGFR) stabilised at 12 months at 52.7 ml/min/1.72m^2^ with RN and 66.8 ml/min/1.72m^2^ with PN [12]. Reductions of renal function to these levels are associated with a 5-year risk of (i) ESKD approaching 1% in both groups [3] and (ii) cardiovascular events of 9.9% and 15.6%, for PN and RN respectively [18, 19]. Although not reproduced in the Van Poppel study, these risks of cardiovascular events are consistent with the 40% increase shown by comparing eGFR > 60 vs GFR = 45–59 ml/min/1.73m^2^ in a longitudinal cohort study that is a seminal paper in the nephology field [20].

Most complications for both PN and RN occur acutely in the peri-operative period, such as bleeding and urine leaks. The main determinants of perioperative complications relate to the anatomy of the tumour—captured and categorised by a number of renal morphometric scoring systems, such as the Preoperative Aspects and Dimensions Used for Anatomic (PADUA) classification and Radius Exophytic/endophytic Nearness Anterior/posterior Location (RENAL) nephrometry score [21, 22]. The main variables determining complexity and risk of complication are size, higher-risk endophytic or favourable exophytic growth pattern, and higher-risk hilar locations next to main feeding vessels versus peripheral locations [8, 23]. Work from our group shows that depending on surgical complexity, moderate to severe complications (Clavien-Dindo 3 or higher) are seen in 4–11% of PN compared with just 2–3% in RN treated by robotic approaches [22]. Acceptable thresholds of complication are not well described, and most studies fail to provide information about the cumulative severity of complications, or inform only on the most severe event, ignoring events of lesser severity.

To define the key parameters for our trial, we undertook detailed surveys and focus groups with key stakeholders (patients, urologists and nephrologists). Patients with lived experience of RN or PN (*n* = 24) agreed that a clinical trial is urgently required to determine which treatment is superior in terms of relative benefits and harms for intermediate sized tumours. They shared that main drivers in decision-making were an intuitive and strong desire to maintain kidney function and avoidance of harm by prioritising being cured of cancer and returning to normal activities as soon as possible. The main drivers for urological surgeons (*n* = 110) considering PN vs RN are potential harms (related to the anatomy of the tumour). Otherwise, there was a strong conviction to save renal function where possible. In cases of T1b tumours (with the solitary exception of hilar endophytic T1b cases) and endophytic hilar T1a tumours, there was equipoise from urological surgeons regarding the best approach. Nephrologists (*n* = 32) chose an eGFR difference of at least 10 ml/min/1.72m^2^ between PN and RN as being a minimal clinically important difference and, triangulating these findings with those from the urologists and patients, informed the design of our trial and its co-primary outcomes.

## Objectives {7}

The aim of this trial is to determine the trade-off between potential benefits, harms and cost between partial nephrectomy compared with radical nephrectomy, for intermediate sized and selected small complex kidney tumours, primarily focusing on renal function and surgical complications over 24 months.

The hypothesis being tested:

Partial nephrectomy for intermediate sized 4–7 cm (T1b) and small < 4 cm (T1a) endophytic (deep-seated) tumours results in better renal function by at least 10 ml/min/1.72m^2^ compared to radical nephrectomy in patients with a normal contralateral kidney.

## Trial design {8}

PARTIAL is a pragmatic patient-randomised controlled, parallel group superiority trial, with an embedded economic evaluation comparing PN and RN for patients with suspected or confirmed renal cell carcinoma (RCC). Patients are approached to participate following informed decision-making and electing for a surgical approach. Patients are allocated to PN or RN in a 1:1 ratio. Trial treatments follow routine clinical management protocols.

The trial includes an internal pilot phase with an embedded mixed-methods process evaluation which aims to identify significant challenges relating to design or conduct that can be addressed and modified before progression to full trial.

## Methods: participants, interventions and outcomes

### Study setting {9}

Participants are recruited from NHS secondary care medium- and high-volume sites in the UK. A list of current trial sites can be obtained from the PARTIAL trial website [24].

### Eligibility criteria {10}

Participating sites are required to have surgeons and surgical teams competent in the delivery of robotic PNs and minimally invasive RNs. Surgeons have completed, as the primary surgeon, more than 30 robotic PNs and 50 laparoscopic or robotic RNs and, at the discretion of the chief investigators, more than 10 robotic PNs per year for the last 24 months. Median length-of-stay and surgical complication rates have to be within acceptable parameters. Individual surgeon data will act as surrogate measures for the entire surgical team.

The inclusion criteria for participants are:Adults ≥ 18 years,Newly diagnosed clinically localised renal cancer (suspected on cross-sectional imaging or histologically confirmed),Local multi-disciplinary review identifying those cases thought suitable for both minimally invasive RN or PN (for minimally invasive, we mean laparoscopic or robotic surgery; cases where open surgery is planned are not eligible),Cross-sectional imaging showing a single tumour, stage T1 (up to 7 cm), where there is equipoise in the multidisciplinary team (MDT) and willingness to recruit into the trial,On imaging, evidence of a radiologically normal contralateral kidney,Patients that have been fully counselled of all the available treatment options (including non-surgical approaches, where appropriate),Able and willing to give informed consent to participate and to participate in trial procedures.

The exclusion criteria for participants are:Solitary functioning kidney,Metastatic disease,Existing CKD (> stage 3b; eGFR < 45),Medically unfit for surgery,Congenital renal abnormality which includes fusion, assent and malrotation,Suspected or confirmed inherited kidney cancer syndrome,Current pregnancy or breast feeding,People without capacity.

Participant eligibility is confirmed by the principal investigator or a medically qualified delegate.

Participants must be eligible for the randomised trial to be eligible for the process evaluation.

### Who will take informed consent? {26a}

Eligible patients are given or sent the Participant Information Leaflet and supplement (the Decision-Making Tool). They have the opportunity to read the Participant Information Leaflet and supplement (the Decision-Making Tool) and discuss the trial with a member of the local trial team before deciding if they wish to take part. Potential participants are given enough time, and as long as they want, to accept or decline involvement. Consent is discussed face-to-face, virtually or by telephone and followed by hardcopy or electronic written informed consent by Good Clinical Practice (GCP) trained members of the local trial team and in accordance with GCP guidelines. Hardcopy written consent may be completed at home by the participant and returned in the post. The member of the local trial team who discussed consent with the participant countersigns the consent form.

The process evaluation component is optional for sites and patients. Data collection includes audio-recording the consultations when site staff (the recruiter) discusses the trial with the patient (to explore opportunities to improve the informed consent discussion), and interviews with patients and site staff (to identify opportunities to improve trial processes). Patients and the recruiter have the opportunity to read a Participant Information Leaflet. A one-off written consent is sought from the recruiter to audio-record the consultation, which covers all audio-recordings made by the recruiter for the trial. The member of the trial office who discussed consent to the audio-recording countersign the consent form. The local trial team seeks verbal consent from the patient to audio-record the consultation. The process evaluation researcher seeks verbal consent from patients and site staff for interviews. Verbal consent is audio-recorded. If verbal consent is declined, the audio-recording is stopped and the file deleted.

### Additional consent provisions for collection and use of participant data and biological specimens {26b}

Participants can opt to be contacted about participating in future long-term follow-up and relevant ethically approved research. Biological specimens are not collected in PARTIAL.

## Interventions

### Explanation for the choice of comparators {6b}

The two surgical technologies being compared are minimally invasive partial nephrectomy (PN) versus minimally invasive radical nephrectomy (RN).

Minimally invasive approaches are laparoscopic or robotic. The robotic approach is a minimally invasive laparoscopic approach assisted by robotic technology. Open approaches are significantly more morbid than minimally invasive approaches and usually reserved for very large or anatomically complex tumours, which are outside the inclusion criteria of our trial.

In the UK, in 2019, for patients with kidney cancers undergoing surgical treatment, there were 3130 RN (73% laparoscopic, 5% robotic, 19% open, 3% n/a) and 1562 PN (76% robotic, 9% laparoscopic 14% open, 1% n/a) as reported in the BAUS Nephrectomy Audit [25] capturing 79% of national activity. In England, in 2019–2023, for patients with kidney cancers undergoing surgical treatment, there were 17,216 RN (57% laparoscopic, 19% robotic, 23% open) and 6665 PN (82% robotic, 5% laparoscopic, 12% open) as reported in the National Kidney Cancer Audit State of the Nation Report 2024 [26]. There is evidence that both laparoscopic approaches, with or without the robot, are broadly similar in outcomes [27].

In the UK, robot access is increasing and the differential costs between laparoscopic and robotic costs are closing, meaning that an increasing proportion of robotic RN and PN is performed [28]. Therefore, to provide a generalisable approach to this pragmatic trial, we include both laparascopic and robotic minimally invasive approaches and exclude those for which open surgery is recommended.

### Intervention description {11a}

Minimally invasive approaches (laparoscopic or robotic) of RN and PN are undertaken in accordance with current NHS standard of care, in patients with diagnosed or suspected localised kidney cancer. RN and PN are performed (or supervised) by delegated surgeons who meet the minimum surgical experience criteria (described in eligibility criteria).

### Criteria for discontinuing or modifying allocated interventions {11b}

Where deemed clinically necessary, the intervention may be converted to an open procedure, or to a treatment different to that allocated at randomisation, or may not proceed at all. Participants who do not receive their allocated treatment are not considered withdrawals and will be followed up for all trial outcomes unless they request otherwise.

Participants are free to withdraw from the trial at any timepoint and can withdraw from participating in the intervention and/or other aspects of the trial. All changes in status, except for the complete withdrawal of consent, mean that the participant is still followed up for all trial outcomes wherever possible.

### Strategies to improve adherence to interventions {11c}

The inclusion criteria for the trial requires the multi-disciplinary team to confirm the participant is suitable to receive both interventions and for the participant to have been counselled of all available treatment options (including non-surgical approaches). The site team records in the case report form if the participant received the procedure allocated by randomisation. Any change from the allocated procedure is recorded with the reason stated.

### Relevant concomitant care permitted or prohibited during the trial {11d}

Participants will be permitted to take part in other non-interventional studies (e.g. questionnaire studies, studies collecting blood/tissue samples or studies investigating aspects of robotic surgery). Patients will be eligible for inclusion in PARTIAL if they are in the long-term follow-up phase of any other interventional trial. People enrolled in the active intervention phase of another interventional trial should be excluded from PARTIAL, except for trials of neo-adjuvant or adjuvant therapy. Participants will receive all appropriate concomitant care during their time in the study; no concomitant care is prohibited.

### Provisions for post-trial care {30}

The interventions are standard of care procedures. The surgery is a single procedure for the participant. At the end of the trial, participants will continue to be monitored as per standard NHS care. If a participant is harmed by taking part in the trial, they have the right to pursue a complaint and seek compensation through the research sponsor of the trial. If a participant is harmed due to negligence, they have grounds for legal action as a patient of the NHS.

### Outcomes {12}

Co-primary outcome measures:
(i)Gains in preserving renal function as measured by eGFR (using the Chronic Kidney Disease Epidemiology Collaboration (CKD-EPI) 2009 formula without the race coefficient as recommended by the National institute for Health and Care Excellence, the UK Kidney Association and European Federation of Clinical Chemistry and Laboratory Medicine [29–31]). The adjusted mean difference between the eGFR score in the PN and RN groups will be analysed to determine if PN results in better maintenance of eGFR compared with RN. This co-primary outcome timepoint is at 2 years post-randomisation, and it will be possible to present effect sizes at all follow-up points using a repeated measures model.(ii)Harms captured by Comprehensive Complication Index (CCI). The CCI is validated in renal surgery [32, 33] and based on the Clavien-Dindo classification (reporting on the most severe event) and is calculated as the sum of all surgical complications that are weighted for their severity [34]. Ideally, the CCI will be analysed as an adjusted mean difference between the PN and RN groups, but the distribution or heteroscedasticity may require a different analysis. This co-primary outcome timepoint is reported at 3 months post-intervention (i.e., collecting events over the peri-operative period after skin closure for the index procedure to three months after surgery).

Secondary outcome measures:Health-related quality of life (HRQoL) captured by the European Organisation for Research and Treatment of Cancer Quality of Life Questionnaire Core 30 (EORTC QLQ-C30) [35] and 36-Item Short Form Survey Instrument (SF-36v2®, Acute version – 1 week recall) [36] participant questionnaires (PQs). The adjusted mean difference in the outcomes between the PN and RN groups will be measured over 2 years post-randomisation, and effect sizes can be presented at all follow-up points using a repeated measures model.Cost and cost-effectiveness captured by quality adjusted life years (QALYs) based on the Short Form 6 Dimension (SF-6D) algorithm and care pathway costs (including complications). The adjusted mean difference between the PN and RN groups will be analysed as incremental cost in UK pounds sterling (£) per QALY gained and reported as additional £ per QALY gained. Estimates will be based on data collected during the 2 years post-randomisation and presented at 2 years post-randomisation.Quality of recovery captured by the 15-Item quality of recovery (QoR-15) [37] PQ (including length of stay) to assess more subtle harms in the peri-operative timeframe from the patient perspective. The adjusted mean difference between the PN and RN groups will be measured over 3 months post-intervention, and effect sizes can be presented at all follow-up points using a repeated measures model.Residual disease captured by rates of positive surgical margin and need for retreatment/surgical revision. The difference between the PN and RN group will be indicated by an odds ratio and presented as the percentage in each surgical margin category. Positive surgical margin will be measured at the point of discharge and retreatment/surgical revision over 2 years post-randomisation.Recurrence-free and overall survival (including local recurrence) captured by cancer-specific survival and all-cause mortality. The difference between the PN and RN group will be indicated by a hazard ratio. The number of recurrences and time to recurrence will be presented for both groups. The summary statistics for the time to recurrence will be the median and quartiles. The outcome will be measured over 2 years post-randomisation.Rates of cardiovascular events captured by non-fatal heart attack, non-fatal stroke and cardiovascular death to assess the correlation between renal function, cardiovascular events and death [17, 19, 20, 38–41]. The difference between the PN and RN group will be indicated by an odds ratio and each event presented by count and percentage. The outcome will be measured over 2 years post-randomisation [17, 19, 20, 38–41].Progression to CKD stages 3, 4 and 5 (end stage renal failure) captured by eGFR. The difference between the PN and RN group will be indicated by an odds ratio and presented by the number of participants and percentage of each group who progress to the three CKD stages during the trial. The outcome will be measured over 2 years post-randomisation.Operative conversion to RN captured by conversion to RN. The outcome will only be observed in the PN group. It will be presented as the number and percentage of participants in the PN group whose surgery is converted to RN. The outcome will be measured before or during the index procedure.Patient acceptability of the intervention was captured by a theory-informed PQ (based on work by Sekhon et al. [42]) in both trial arms at 3 months post-intervention. Post-randomisation crossovers and preferences identified in screening logs will also be monitored during the trial to develop solutions to enhance recruitment as part of the embedded mixed methods trial process evaluation.

Long-term objectives:Participants can consent to potential future follow-up, through efficient means (such as routine data) as part of a separately funded study, allowing correlations of renal preservation with cardiovascular events, survival (cancer-specific, recurrence free and overall survival) and ESKD at 5–10 years.We aim to establish a well-characterised cohort of patients with RCC including clinical data, urine, blood and tumour specimens for future studies (based on separate funding).The core outcome sets (COS) for renal cancer [43] are currently being developed by other teams and due to complete within the lifetime of PARTIAL. Outcomes identified from the COS will be incorporated (where able) into PARTIAL data collection.

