Based on Mayo Scoring System, rates of metastatic recurrence over 3 years for low-risk (most T1a/T1b) tumours are 2.1% [50]. In a contemporary series comparing PN with RN for T1b, 5-year metastases rates were 8.2% and 12.8%, respectively [51]. Nevertheless, survival rates for localised T1b renal cancer remain high with over 5-year cancer-specific survival rates for PN = 97.6% and RN = 95.5% [51]. Also, 2-year overall survival rates in the Van Poppell study were > 95% for both PN and RN [13]. Therefore, we do not anticipate any emerging patterns of differential outcome on the main measures of interest due to few events at 2 years.

For the process evaluation interviews, approximately 15 interviews per group will be conducted for participants who consented to the RCT and patients who did not consent to the RCT. A minimum of 15 clinical and recruitment staff at a minimum of 7 participating centres will also be interviewed. Sampling will be informed by Francis et al. [52]. All staff involved in discussing the PARTIAL trial with potential participants will be asked to routinely record consultations in which the trial is discussed.

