**Assessments:**									
Baseline characteristics	X								
Renal function: eGFR^a^	X		X	X		X	X		X
Quality of life: EORTC QLQ-C-30, SF-36	X		X	X	X	X	X	X	X
Participant cost questionnaire	X					X	X	X	X
Participant time and travel							X		
Comprehensive Complications Index					X				
Quality of recovery: QoR-15			X	X	X				
Late complications						X	X	X	X
Cardiovascular events									X
Recurrence^b^									X
Further treatment									X
Surgical details & resource use		X							
Pathology & positive surgical margins		X							
Patient acceptability					X				

*eGFR* estimated glomerular filtration rate, *EORTC QLQ-C30* European Organisation for Research and Treatment of Cancer Quality of Life Questionnaire Core 30,
*QoR-15* 15-Item quality of recovery scale, *R0* date of randomization, *SF-36* 36-Item Short Form Survey Instrument, *S0* date of surgery

^a^There are preferable measurement windows for eGFR at key timepoints: 1 week post-surgery (within 1 week of surgery); 1 month post-surgery (± 1 week); 6 and 12 months post-randomisation (± 1 month); 24 month post-randomisation (± 3 months). All eGFR tests, including out of window observations, are recorded

^b^This outcome is not collected in participants who do not have confirmed renal cell carcinoma (RCC)

At baseline, the local research team captures baseline demographic and clinical information, including baseline renal function (eGFR) and tumour size and surgeon assigned location parameters (for PADUA classification [21]). Participants are asked to complete a baseline questionnaire prior to randomisation. During follow-up, the local research team collects outcomes from participant medical notes.

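### Recurrence-free survival is defined through two death measures, its hazard ratio names no event, and a median with quartiles does not suit a recurrence rate of a few per cent

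*Protocol article*

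**What the plan says.** All references are to the protocol article.

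- **Outcomes {12}, secondary outcomes, definition:** "Recurrence-free and overall survival (including local recurrence) captured by cancer-specific survival and all-cause mortality".
- **Same item, effect measure:** "The difference between the PN and RN group will be indicated by a hazard ratio". No event is named.
- **Same item, reporting:** "The number of recurrences and time to recurrence will be presented for both groups", and then "The summary statistics for the time to recurrence will be the median and quartiles". The follow-up is fixed: "The outcome will be measured over 2 years post-randomisation".
- **Long-term objectives, same section:** cancer-specific, recurrence-free and overall survival are listed as three separate outcomes.
- **Table 1:** recurrence has its own row, marked once, at 24 months after randomisation. A footnote restricts it: "This outcome is not collected in participants who do not have confirmed renal cell carcinoma (RCC".
- **Sample size {14}:** "rates of metastatic recurrence over 3 years for low-risk (most T1a/T1b) tumours are 2.1" per cent. A T1b series is cited with 5-year metastasis of 8.2% (PN) and 12.8% (RN) and 5-year cancer-specific survival of 97.6% and 95.5%. In an earlier randomised trial, 2-year overall survival was above 95% in both groups. The authors expect no differing pattern "on the main measures of interest due to few events at 2 years".

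**The concern.** The label and the measures do not match. Cancer-specific survival ends at a cancer death and all-cause mortality at any death. A patient who recurs and is alive at 2 years is an event in neither, although the same sentence says local recurrence is included. The hazard ratio that follows could be for recurrence, recurrence or death, cancer death, or any death. These are different quantities, and the text does not choose among them.

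The second difficulty is the summary. A median and quartiles suit an outcome that most participants reach. Here the document itself expects few events.

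Cancer control is one side of the trade-off that the trial sets out to measure. The Introduction associates PN with higher recurrence and reports that patients gave priority to being cured. If the definition is followed literally, the survival comparison leaves out most of the events that matter for that question.

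**Working it through.** **Number at risk.** The document gives no event count or power for recurrence, so the only stated figure to reproduce is the trial size. With SD 16, a 95% CI no wider than 7 and 90% assurance, the smallest n per arm is 178 (assurance 0.908), as stated. Allowing for 15% attrition, 356/0.85 = 419, against 420 stated. That gives about 210 randomised per arm.

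**What the death measures leave out.** From the 5-year figures in Sample size {14}, taking every cancer death to follow a metastasis:

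- PN: cancer death 100 − 97.6 = 2.4%, metastasis 8.2%. Share missed = 1 − 2.4/8.2 = 71%.
- RN: cancer death 100 − 95.5 = 4.5%, metastasis 12.8%. Share missed = 1 − 4.5/12.8 = 65%.

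All-cause mortality adds deaths from other causes but no recurrence in a living patient.

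**Recurrence at 2 years.** At constant hazard, p(2) = 1 − (1 − p)^(2/T):

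| Source rate | 2-year proportion | Events in 210 |
|---|---|---|
| 2.1% at 3 years | 1 − 0.979^(2/3) = 1.4% | 3.0 |
| 8.2% at 5 years (PN) | 1 − 0.918^0.4 = 3.4% | 7.1 |
| 12.8% at 5 years (RN) | 1 − 0.872^0.4 = 5.3% | 11.2 |

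The trial total is therefore between 420 × 0.01405 = 5.9 and 7.1 + 11.2 = 18.3 events. Linear scaling gives nearly the same proportions (1.4%, 3.3%, 5.1%).

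**Median and quartiles read as survival quantiles.** The lower quartile needs 25% with an event and the median 50%. At constant hazard the times are T·ln(0.75)/ln(1 − p) and T·ln(0.5)/ln(1 − p):

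- 2.1% at 3 years: 40.7 and 98.0 years.
- 8.2% at 5 years: 16.8 and 40.5 years.
- 12.8% at 5 years: 10.5 and 25.3 years.

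Follow-up is 2 years. If deaths are added at 5%, the bound implied by the cited overall survival, the event proportion is at most 5.3 + 5 = 10.3% per arm. At that rate the chance of 53 or more events in 210 (25%) is about 7 in 10 billion. The rates cover metastasis only and the document gives none for local recurrence, but total recurrence would have to be 25/5.3 = 4.7 times the highest converted rate to reach the lower quartile.

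**Median and quartiles read as a description of those who recur.** They can then be calculated, from about 3 to 11 times per arm. They condition on an event after randomisation and ignore censoring.

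**Hazard ratio.** With d events the 95% CI runs a factor exp(1.96 × 2/√d) either side: 4.95 at d = 6 and 2.52 at d = 18.

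**Participants without confirmed cancer.** Recurrence is not collected in them, and the document gives no figure for how many there will be. The event counts fall in proportion to their share; the percentages among confirmed cases do not change.

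**The case against.** The strongest reply is that the intention is clear enough. The defining sentence mentions local recurrence, Table 1 collects recurrence as its own item, and the number of recurrences is promised for both groups. The long-term objectives keep the three survival outcomes apart, so the authors do not confuse them. Event definitions, censoring and competing risks are commonly left to the SAP. The median and quartiles follow directly on the count of recurrences and can be read as a plain description of observed times, in which case the 25% threshold does not apply. Low precision is conceded in Sample size {14}.

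Much of this stands, and it rules out three stronger readings. A reader might infer that the recurrence outcome cannot be computed; it can, because the data are collected. A reader might infer that the report will not show how many patients recur; the document promises that number. A reader might infer that the arms will be compared on their medians; the stated between-group measure is the hazard ratio. The wide hazard-ratio interval is no fresh defect either, since few events are acknowledged.

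Two points remain. An SAP can add detail to a definition, but here the protocol names measures that do not match the label and leaves the hazard ratio without an event. And the descriptive reading makes the median computable but not informative, because it describes a handful of people selected by outcome.

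**Conclusion.** The point holds as a misdefinition of one secondary outcome together with an ill-suited summary. Using cancer death in place of recurrence would lose about two thirds of metastatic recurrences on the document's own 5-year figures. The median and quartiles are out of reach as survival quantiles by a wide margin, or rest on about 3 to 11 recurrers per arm.

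The event figures rest on a constant hazard, on rates for metastasis only and on 210 participants per arm. The document states no 2-year recurrence rate: 1.4-5.3% is derived. Local recurrence would add some events and exclusion of participants without confirmed cancer would remove some. Neither is likely to alter the conclusion, given the distance from 25%. The co-primary outcomes, the sample size and the data collected are not affected. The change should be made before analysis.

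**What to change.** 1. Define recurrence-free survival as time from randomisation to the first of local recurrence, distant recurrence or death from any cause.
2. List overall survival and cancer-specific survival as separate outcomes, and give each of the three its own hazard ratio with the event named.
3. Replace or supplement the median and quartiles with the 24-month cumulative incidence of recurrence in each arm, with death as a competing event, and the between-arm difference with its 95% CI.
4. State how participants without confirmed renal cell carcinoma enter: for example, whether the recurrence analysis is restricted to confirmed cases, or whether they are kept and contribute only deaths.

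The cost is a few sentences in the protocol and SAP. Recurrence is already collected, and the promised time to recurrence and mortality outcomes already need the dates. With few deaths, the competing-risk estimate will differ little from a simple proportion; the gain is a named event and an absolute difference with an interval. Last follow-up is expected in September 2028, so there is time.
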